## Abstract

Background: Oral diseases represent a constant burden for health care and socio-economic systems as they are correlated to other non-communicable diseases. The aim of the proposed intervention is to test the effect of daily tooth brushing and oral health education on the oral health status of kindergarten children. Methods: The protocol will be conducted based on a previous epidemiological survey and conducted over 24 months; it has been developed on different levels. Dental hygienists will receive specific training to deliver oral health promotion to children and nursery educators. Training will focus on tailoring key messages to the specific age at visit; this will be outlined in the care pathway and offer practical preparation for delivering interventions and a toothpaste/toothbrush scheme. It will also, involving involve offering free daily tooth brushing to every 4–6-year-old child attending nursery. Data will be collected in four kindergartens in the capital or metropolitan areas, two kindergartens each in two large cities, and one kindergarten each in four villages from different geographic areas. Procedures used to assess the outcomes of each activity will be tailored to specific outcomes. Daily tooth-brushing activities will be monitored using qualitative research. A cost analysis including the distribution of necessary materials and correct delivery of products that shows price trends and percentage differences over the time span as well as consumer price index evaluation for the given time span will be conducted. Clinical outcomes will be evaluated using the caries incidence rate; this will be calculated for each tooth as the unit of analysis and evaluated using a multi-step approach. Discussion: Downstream oral health prevention interventions, like clinical prevention and oral health promotion, aim to enhance children’s quality of life. The program’s goal is to progress towards upstream interventions for a more significant impact.

## 1. Introduction

The 74th World Health Assembly recognized oral diseases as strictly correlated to other non-communicable diseases. Oral diseases represent a constant burden for both health care and socio-economic systems [1]. Dental caries and periodontal disease are the major oral diseases worldwide. In children under the age of 6, the disease, called Early Childhood Caries (ECC), occurs in children under the age of 6 and has a specific pattern that leads to significant modifications in the child’s functional development [2]. The disease is, nowadays, considered reversible if it is diagnosed in the early, non-cavitated stage, and can be halted even if indicators suggest microcavitation of the enamel. However, it remains the most common chronic disease in young children, and it has also been associated with poor quality of life for both affected children and their parents, affecting their ability to learn, causing missed school days, and incurring high costs for treatments [3]. The presence of ECC in very early childhood is linked to a higher risk of developing new caries lesions in the permanent dentition and an increased number of emergency dental visits due to caries complications [4].

Good behaviors and skills gained during early childhood are crucial for maintaining good oral health throughout life [4,5]. In addition to oral hygiene, there are several other factors that influence oral health status, such as attending dental visits, socio-economic status, or parental dental attendance, especially maternal attendance [4,5,6]. During adult life, healthy hygiene behaviors such as tooth brushing and additional dental hygiene measures are correlated to dental visits, dental plaque accumulation, the presence of calculus, and dental anxiety [7].

The scientific literature provides extensive evidence of oral health inequalities due to specific oral health behaviors, such as dietary habits, hygiene practices, bad habits, and dental check-ups [6,8,9]. This dynamic process, which has been extensively studied using the life course framework, involves a number of variables. Oral health status was linked to several covariates, such as socio-economic status, maternal dental visit behavior, and local risk factors, such as the presence of plaque, calculus, dental anxiety, and oral hygiene patterns, such as tooth-brushing frequency and use of additional hygiene products [8]. In addition, lower attendance to dental care services can be seen among younger children, edentulous patients, patients who suffer severe tooth loss, and have poor health literacy, as well as those with general and oral health issues [9]. However, these findings are mainly cross-sectional rather than longitudinal. Oral health interventions are often not a priority for medical staff and health policy developers in several countries, with other diseases considered more important. Another issue is that there are insufficient evidence-based interventions that address preventive dental care and oral health risk factors [10,11].

The effectiveness of oral health interventions should focus on the fact that even simple interventions can be influenced by multiple individual factors, including social determinants and health systems. Therefore, they should be considered complex interventions [12].

The evaluation of complex oral health interventions is often difficult because of the complex mechanisms involved in the processes. Therefore, rather than attempting to evaluate the effectiveness of the intervention without taking into account all the covariates, research should focus more on evaluating methods of implementation, appropriate target populations, and requirements that need to be met before application. To implement an intervention, details regarding feasibility, steps, and working components should be first considered.

Several guidelines and frameworks for the development, implementation, and evaluation of health interventions have been published by other countries like Scotland (“Childsmile”), Wales (“Designed to smile”), Brazil (“Brazil Sorridente”) [13,14,15], but data on preventive oral health interventions are still scarce. Thus, the design proposed for this intervention focuses on the details of the development and implementation of an oral health intervention for young children.

### 1.1. Objectives

The null hypothesis is that daily tooth brushing and oral health education in kindergartens have no effect on the caries status of children aged 4-6. To test the hypothesis, the project will aim to establish the association between those variables. Ancillary objectives will be to improve oral health and reduce inequalities in both dental health and access to dental services by shifting the balance of care towards more preventive and anticipatory care and promoting health improvement.

### 1.2. Expected Outcome

The clinical relevance of the findings is that preventive care includes good oral health behaviors such as low sugar consumption, health education, and daily oral hygiene using a toothbrush and fluoride toothpaste, as well as additional aids such as interdental brushes, dental floss, or mouthwashes that can help remove plaque and disrupt biofilm.

## 2. Experimental Design

The study is designed and planned as an RCT, taking into consideration the early diagnosis of caries lesions through clinical examinations in the nurseries, control of risk factors through the evaluation of oral health-related knowledge, and behaviors, health education, and evaluation of the efficacy to arrest caries’ progression through the application of fluoride toothpaste. The trial will also develop new primary care teams—dental hygienists. This will provide a framework for integrating the prevention and control of dental caries into general health interventions.

In accordance with the informed consent, all personal data of the participants will be kept anonymous. The participants will receive a unique ID which will be used for data entry on an online software. The ID will be used for each clinical examination and data will be entered accordingly. As stated by Romanian regulations, an archive of the data has to be kept for 5 years after the trial in the secured archive of the university. The program was approved and registered by the Ethical Committee of the “Victor Babes” University of Medicine and Pharmacy Timișoara, Romania, under trial No. 18688/23.10.2023 and Protocol NCT06441500/28.05.2024 released on https://clinicaltrials.gov/, accesed on 29 May 2024, protocol version 1.

The project will be implemented in collaboration with the universities of Medicine and Pharmacy in Bucharest, Timișoara, Cluj-Napoca, Craiova, Iasi, and Targu Mures in order to ensure a homogeneous distribution of the evaluation sites, covering the whole country. The study group will consist of kindergarten children. The pathfinder sampling technique will be used to obtain a representative sample. Selection of nurseries will be performed according to the pathfinder sampling technique. As suggested by the World Health Organization (WHO), this survey’s design is suitable for the collection of data for planning purposes and monitoring of oral health programs in all countries regardless of the level of disease, availability of resources, or complexity of care.

The number of children is based on an initial calculated requirement of 415 participants, with an additional 10% (rounded up from 456.5 to 460) added to account for potential dropouts or loss to follow-up. The sample is stratified based on administrative units and locality type and randomization is ensured by using the MS Excel function. Children will be included based on the enrolment in kindergarten, consent of the parents, and assent from the child. The exclusion criteria are represented by chronic general diseases or a history of allergic reactions, the presence of fluorosis or other enamel deficiencies, and non-collaborative behavior. The selection can be seen in the flowchart in Figure 1.

The nationally representative sample will be evaluated at baseline using self-assessment tools and clinical examination. During the intervention, evaluations will be performed every 6 months.

The program is designed to deliver additional clinical prevention activities through dental hygienists, aimed at children aged four to six, a special priority being afforded to nursery establishments, in order to improve the oral health of young children and complement the established national toothpaste/toothbrush scheme. The activity flow chart can be seen in the figure below (Figure 2).

### Study Setting

The total sample size is calculated according to the WHO guidelines using a stratified sampling technique for examination sites in Romanian cities: Bucharest, Timișoara, Cluj-Napoca, Craiova, Iasi, Targu Mures, and the surrounding geographical areas. Data collection points (Figure 3) will be 4 kindergartens in the Capital or metropolitan areas, 2 kindergartens in each of 2 large cities, and 1 kindergarten in each 4 villages from different geographic areas (Dobrogea, Moldova, Ardeal, Muntenia). Metropolitan areas in Romania are Iași, Brașov, Oradea, Târgu Mureș, Cluj Napoca, Craiova, Roman, Baia Mare, Satu Mare, Timișoara and Arad. Romania is divided into 40 counties (regional administrative sites consisting of several cities and villages), the capital, Bucharest being considered on its own. Further on, it is divided into metropolitan areas (over 250,000 inhabitants), large cities (100,000–250,000 inhabitants), small cities (less than 100,000 inhabitants), and villages (less than 5000 inhabitants). A detailed list of the study sites can be obtained from the project manager.

Children aged 4–6 years, enrolled in kindergartens in Romania will be included in the study, providing they show signed informed consent from their parents/caregivers. Parents or caregivers are responsible for signing the consent form for children and any subject may withdraw from the study at any time after recruitment. The examiners shall collect the informed consent forms prior to the examination. Before each examination, each subject will have the free will to participate by direct inquiry.

## 3. Procedure

Pre-intervention baseline data will be collected according to the WHO stepwise approach—self-assessment and collection of clinical data will be used to plan and evaluate further health interventions. Self-assessment information on children’s oral health behaviors, like diet, frequency of brushing, use of fluoridated toothpaste, use of additional oral hygiene aids (interdental brushes and mouthwash), frequency of dental check-ups, and reason for last dental visit, will be collected using the previously developed National Oral Health Survey questionnaire [15]. Answers will be obtained from parents/caretakers before clinical examination. In the unlikely case that no family member or tutor will be able to read the questions, they will be assisted by the educators. The working tool consists of 15 items that make up the two dimensions of types of behavior (prevention and nutrition) and family characteristics (parent’s level of education and working status). The two behaviors will be correlated with clinical indices that will help to delimit the existence or lack of certain significant differences among children. In a concrete way, for a better understanding of the risk factors, the scientific approach aims to relate to not only specific elements of the child (gender, age, parental education, and environment of residence), but also elements related to the objective reality in which the child lives (development index and development region of the county where the child comes from, type of city, etc.). Reexamination will be performed twice a year to ensure data comparison.

Clinical examinations will be performed using the International Caries Detection and Assessment System (ICDAS) criteria by a calibrated medical staff from each partner‘s university. ICDAS represents a caries detection and assessment system that quantifies caries lesions into 6 categories: code 1 represents demineralized lesions (white spot lesions) which can be only seen after air-drying the surface for 5 s; code 2 are demineralized lesions that can be observed without air-drying; code 3 are micro-cavities in enamel; 4 are lesions in dentin, observed as a dentinal shadow; and 5 and 6 are already cavitated lesions which affect less or more than half of the tooth surface. Calibration will be performed every six months according to the ICCMS (International Caries Classification and Management System) guidelines calculating the intra- and inter-examiner correlation coefficients (kappa-index). The level of agreement has to be more than 80%. Children will be examined in a seated position, using a dental mirror and a probe, without air-drying. Thus, ICDAS codes 1 and 2 will be counted together as “A”.

Volunteer dental hygiene students will be trained to deliver oral health promotion to nursery educators and oral health promotion activities for children, focusing on the tailoring of key messages to the specific age and on practical preparation for delivering interventions in nurseries along with implementing the toothpaste/toothbrush scheme involving free daily tooth brushing to every 4 and 6-years old child attending nursery. The Bass brushing technique will be taught to the children and they will brush their teeth once a day while present in the kindergarten. The technique has been chosen because it was proven to be the most effective method in young children [16,17,18]. Fluoridated toothpaste will have a concentration of 1000 ppm Amin fluoride.

Children will receive educational lessons using PowerPoint presentations on a regular basis. Educators will be provided with brochures containing information on the tooth-brushing technique as well as oral health education: healthy diet, proper oral hygiene, frequency of dental check-ups, etc.

A detailed participant timeline is presented in Table 1.

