### 3.3. Assignment of Interventions

In order to create a nationally representative sample, the public information available on the websites of all County School Inspectorates (41 counties plus the Romanian Capital) was analyzed. This process involved the evaluation of publicly available information from 4696 schools, which aided the understanding of the territorial distribution of the target population.

The national representative sample is stratified and randomized. The stratification was performed at the level of administrative units (counties), and on locality type (i.e., urban versus rural localities). For each county, the total number of pupils and the percentage of children for each of these administrative units were computed. The percentage was used to estimate how many children would have to be included in each county. The number was then divided based on locality type (i.e., urban versus rural), and the final target number of evaluations was obtained. The MS Excel’s randomization function was used for each county to select an urban and a rural nursery.

The steps of the allocation sequence are as follows:The order of the counties is decided—each collection point receives several counties and the research team can decide in which county it would be more convenient.Kindergartens in the respective county are contacted to determine their availability to participate in the study and the number of children from the target population available for evaluation.If the 2 kindergartens that are contacted together have at least 18 children (out of the required 25), data collection can begin in the respective county.

If the 2 kindergartens contacted do not have at least 18 children together, the next county on the list will be selected and the procedure returns to steps 2 and 3.

E-mails will be sent to the correspondence address provided to generate the allocation sequence. Consent in principle and an estimate of the number of children in the target population will be requested. If there is no response within the next 5 working days, the kindergarten will be called in to check that the e-mail was received in good condition (e.g., to obtain a working e-mail address or to see the status of the request).

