### 3.5. Statistical Methods for Primary and Secondary Outcomes

Caries activity levels after implementing the daily tooth-brushing scheme will be evaluated as the primary outcome. The outcomes will offer information regarding the particularities of the clinical investigation for the specific age group and the time necessary for the investigation and intervention. Clinical outcomes will be evaluated by using the caries incidence rate, calculated on each tooth as the unit of analysis and evaluated using a multi-step approach:

The net caries increment for initial, moderate, and extensive caries severity using ICDAS (Δ-initial, Δ-moderate, and Δ-extensive) will be calculated at each follow-up examination.

Events will be defined as a tooth receiving a lesion or as the sum of the Δ-caries changes in status recorded at the baseline examination, at the interim, and at the last examination. The number of events will be appraised by subtracting the number of caries-free teeth at the last examination from those at baseline.

Data analysis will be performed using SPSS version 24 (IBM Corp., Armonk, NY, USA) and the R software (R Core Team 2023). SPSS will be used for initial data cleaning, descriptive summaries, and basic inferential tests. R will be used for advanced modeling, intention-to-treat (ITT) analyses, and reproducible visualizations.

Data will be cleaned and validated prior to analysis. Descriptive statistics will be computed using continuous variables—mean ± SD (if normal), or median [IQR] (if non-normal) and categorical variables—counts and percentages. Baseline comparability between groups will be assessed but not tested for statistical significance (in accordance with CONSORT guidelines) [19]. Primary outcomes will be analyzed using the intention-to-treat (ITT) principle. The choice of statistical test depends on the outcome type. For continuous outcomes, linear regression adjusting for baseline, if available, will be used. Logistic regressions will be performed for binary outcomes and Poisson or negative binomial regression could be used for count data. For the longitudinal data, linear mixed models or generalized estimating equations (GEE) will be used to account for within-subject correlation. To explore relationships between secondary variables, correlation analysis will be performed.

The non-parametric Mann–Whitney U test will be applied to assess the differences across the mean number of events between groups.

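### Examining team and region very probably coincide, so the planned regional and development-index comparisons of caries levels cannot be told apart from differences between examiners

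*Protocol article*

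**What the plan says.** All references are to the protocol article.

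- **Who reads.** Section 3 (Procedure) assigns ICDAS examinations under "criteria by a calibrated medical staff from each partner‘s university". Section 2 (Experimental Design) lists six partner universities, chosen "in order to ensure a homogeneous distribution of the evaluation sites, covering the whole country".
- **Where they read.** Section 3.3 states that "each collection point receives several counties and the research team can decide in which county it would be more convenient". The Data Availability section gives each partner access to the data it collected itself.
- **Safeguard.** Section 3 requires calibration every six months, "calculating the intra- and inter-examiner correlation coefficients (kappa-index"), and sets a threshold: "The level of agreement has to be more than 80" per cent.
- **Regional use of the data.** Section 3 relates clinical indices to, among other things, the "development index and development region of the county where the child comes from". Section 4 (Expected Outcomes) plans to assess regional differences through the County Development Index and ties this to the programme's efficacy at national level.
- **Named analyses.** Section 3.5 gives, for continuous outcomes, "linear regression adjusting for baseline, if available, will be used". It also names mixed models or GEE for within-subject correlation, a Mann–Whitney test of events between groups, and Cox models whose factors are not listed. No examiner, university or centre term is named.

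**The concern.** If each university's staff examine only that university's counties, every difference in reading habit between teams is also a difference between sets of counties. A team that scores early lesions more readily makes its area look worse. This is a measurement problem. It is separate from the fact that region is not randomised, and it would remain if the regions were identical in true disease.

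Early lesions are where readings are most likely to differ. Children are examined without air-drying, codes 1 and 2 are pooled, and initial lesions enter the increment.

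At stake is the reading of the regional and development-index results, which the protocol wants to use for a national conclusion and roll-out. The same team effect also enters the comparison of groups, but its size there depends on how the arms lie across universities.

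**Working it through.** **1. Is team aliased with region?** Three statements point the same way: examiners come from each partner university (Section 3), each collection point receives its own counties (Section 3.3), and each partner holds the data it collected (Data Availability). In Section 3.3 a collection point cannot mean a kindergarten, because it receives several counties and has a research team that chooses among them. The nesting is a strong inference and is not stated outright.

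**2. What does the calibration rule allow?** Suppose one examiner calls a share p of teeth carious and a second calls p + d, with every disagreement in the same direction. Then Po = 1 − d and Pe = p(p + d) + (1 − p)(1 − p − d). Setting kappa = (Po − Pe)/(1 − Pe) = 0.80 gives

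d = 0.4·p(1 − p) / [1 − 0.2(1 − 2p)].

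| Prevalence p | d | Teeth out of 20 |
|---|---|---|
| 0.10 | 0.036/0.84 = 0.043 | 0.9 |
| 0.30 | 0.084/0.92 = 0.091 | 1.8 |
| 0.50 | 0.100/1.00 = 0.100 | 2.0 |

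These are worst cases: binary scoring, agreement exactly at the threshold, and all disagreement one way. The protocol mentions kappa and then a percentage. If the 80% is raw agreement, d can approach 20% of teeth. The prevalences and the 20 teeth are assumptions.

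**3. What could that do to a comparison across the teams' areas?** The protocol gives no between-team variance, so this is an illustration over a range. Take six universities with 77 children each (460/6 = 76.7), the protocol's SD of 2, no true regional difference, and a team shift of SD s teeth. A one-way F test has its between-team mean square inflated by k = 1 + 77s²/4, and rejects with probability P(F > 2.234/k) on 5 and 456 degrees of freedom. In the last column the protocol's design effect of 2 is put into the error variance, so that k = 1 + 77s²/8.

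| Assumed s (teeth) | Rejection, independent children | Rejection, design effect 2 |
|---|---|---|
| 0 | 5% | 5% |
| 0.1 | 10% | 7% |
| 0.2 | 28% | 16% |
| 0.3 | 54% | 31% |
| 0.5 | 86% | 66% |

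The plan does not name a test across universities. The table applies to the extent that its regional comparison contrasts areas read by different teams.

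**4. The group comparison.** The plan's own figures come first. 415 × 1.10 = 456.5, rounded to 460 in the protocol. No mean difference is stated. Solving back with 207.5 per arm gives √[2 × 2 × (3.24 × 2)²/207.5] = 0.90. The standard error is then √(2 × 2 × 4/207.5) = 0.278, and power is Φ(0.90/0.278 − 1.96) = 90%.

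With arms balanced inside each university, the team effect adds no bias. Left in the error term, it gives a standard error of √[2 × 2 × (4 + s²)/207.5]:

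- s = 0.3: 0.281, power 89.3%
- s = 0.5: 0.286, power 88.2%

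Here s is the part of the team difference that survives in the change score. A constant additive difference cancels from net change if the same team re-examines, so only drift, or a difference that is not constant, remains.

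**5. Is a within-team contrast feasible?** Section 3.3 asks for 25 children per county. 400/25 = 16 and 460/25 = 18.4, so 16 to 18 counties, or about three per university. The 12 kindergartens in the Study Setting section (4 + 4 + 4), taken two per county as in Section 3.3, would instead give six counties and perhaps one per team. The contrast exists under the first reading and may vanish under the second.

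**The case against.** **The article is only silent on model terms.** It lists families of methods, leaves the Cox factors open, and refers to further details of the analysis plan. A centre term may sit there. This is fair, and the missing term alone would be no finding. What stands is that the article itself fixes who reads, where they read, and a regional comparison with a national conclusion attached. It also names a plain Mann–Whitney test, which has no place for such a term.

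**The nesting is inferred.** Correct, and the point is worded accordingly. Elsewhere the article uses data collection points for kindergartens, but that meaning does not fit Section 3.3.

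**Calibration already deals with this.** It limits the difference and targets drift. An agreement threshold says nothing about direction, so a systematic shift can pass.

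**A development-index slope is biased only if team shifts correlate with the index.** True, and no such correlation is shown. With only six teams, however, chance alignment is not averaged away.

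**A stronger reading is tempting:** that examiner differences bias the trial's group comparison or cost it much power. The document does not support this. It does not say how arms are spread over universities, and its primary outcome is change, from which a constant shift cancels. One can construct a fall in power to 63%, but this needs 12 kindergartens split 6/6 without regard to team and an assumed team SD of 0.5 tooth in change. It may also count some variation twice: with 25 children per kindergarten, a design effect of 2 implies an ICC of 1/24 = 0.042 and a between-kindergarten SD of √(0.042 × 4) = 0.41 tooth, which can already include shared reading differences.

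**Conclusion.** The point holds for regional, development-index and risk-factor comparisons of caries levels. Team and region are very probably aliased, and nothing stated in the plan separates them. The calibration rule leaves room for a one-directional difference of up to 0.9 to 2.0 of 20 teeth under the worst-case kappa reading. Followed as written, the plan could report an examiner difference as a regional one. How often depends on a between-team SD that the protocol does not give: for 0.2 to 0.3 tooth, the illustration gives 28% to 54% with independent children and 16% to 31% with design effect 2, against a nominal 5%.

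For the group comparison, a university stratum is a modest gain in precision and a guard against imbalance. It does not correct a demonstrated bias. Under balance the power loss is under 2 points for team SDs up to 0.5. If arms were unevenly spread (70/30 in three universities, 30/70 in the others), simulated type I error was 8% at s = 0.3 and 13% at s = 0.5, but the protocol gives no ground for assuming that spread.

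**What to change.** 1. Record the examining university and the examiner at every examination, from baseline on.
2. Keep the same team for a county at every visit, so that a constant reading difference cancels from change.
3. Include examining university in the development-index, region and risk-factor models (fixed, or random if clusters are few), so that contrasts are between counties read by the same team.
4. Report differences between universities' regions as not separable from examiner team.
5. In the group comparison, use examining university as a stratum where both arms occur within a university: for example, a stratified rank test in place of the plain Mann–Whitney, or a centre term in the regression.
6. State whether the 80% threshold is kappa or raw agreement.

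**Cost.** Two recorded fields and one model term, with no extra examiners. The term uses up to 5 degrees of freedom and makes the development-index slope less precise. If only one county per team is enrolled, that slope cannot be estimated within teams at all. A university with all its kindergartens in one arm contributes nothing to a within-team group contrast. Claims about differences between regions read by different teams have to be given up; separating the two would need cross-team re-examination of a subsample, which is extra fieldwork.
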